### Measurements

The screening procedures included biometric measurements and blood sample collections. The biometric measurements were height, weight, hip and waist circumference, and blood pressure. Non-fasting venous blood samples were analyzed for HbA_1c_, plasma glucose, hemoglobin, total cholesterol, triglycerides, LDL, HDL, and circulating estradiol.

### Biometric Measurements

The biometric measurements were measured through the following protocols. Weight was measured using a standardized scale with participants wearing light clothing and no shoes. Height was recorded with participants standing straight against a wall-mounted measuring tape without shoes. Waist circumference was measured 5 cm above the center of the navel and hip circumference at the widest part of the hip, both using a stretch-resistant tape, ensuring the tape was parallel to the floor and snug but not compressing the skin. Blood pressure was measured using a calibrated cuff on the upper arm after participants had rested for 5 minutes, with three consecutive readings taken with the participant seated both feet on the floor and both arms on their legs.

### Blood Samples

Nonfasting venous blood samples were analyzed by the Department of Clinical Biochemistry, AUH for levels of HbA_1c_, glucose, total cholesterol, triglycerides, LDL, HDL, estradiol, and sex-hormone binding globulin. The blood samples were destroyed immediately after analysis. Results outside standard values were reviewed by consultant physicians and patients, and their general practitioners were notified with follow-up recommendations when necessary.

### Data Collection and Management

Information on patient demographics, treatment modalities, and cancer-specific characteristics were collected through a manual search of electronic medical journals, including pathological records. All data were securely stored in a RedCap database hosted by Aarhus University.

To promote participant retention and ensure complete follow-up, the 3-month appointments were booked by hospital secretaries as part of routine care. If a participant was not scheduled for a follow-up appointment, trial personnel proactively contacted the participant to arrange the study visit. If participants discontinued ET, outcome data were still be collected at the 3-month follow-up visit, unless consent was withdrawn.

### Cohort Size

The study aimed to include 112 participants over the six-month enrollment period. The target was based on an annual referral rate of approximately 360 patients to the Department of Oncology, AUH, for adjuvant systemic therapy, of which approximately 90% were eligible for ET due to ER+ EBC, and assuming a 70% participation rate among eligible patients.

Statistical power calculations supported the sample size. Based on a comparable study with a similar population [30], where the standard deviation of the change in BMI over 3‐5 years after diagnosis was 3, a cohort of 112 participants provides >80% power to detect a true change in BMI of 0.8 kg/m^2^ at a 5% significance level. Furthermore, other studies have found larger BMI changes over shorter periods. For instance, Heideman et al observed a mean BMI change of 2.0 kg/m^2^ (± 4.9) after one year, with 26% of patients gaining ≥5 kg following adjuvant treatment [31].

### Statistical Analysis

#### Definition of Analytic Values

BMI will be calculated as weight (kg)/height^2^ (m). WHR will be calculated as waist circumference divided by hip circumference. Blood pressure will be calculated as the average of three measurements. Middle arterial pressure will be calculated as 2 times diastolic blood pressure added systolic blood pressure divided by 3.

MetS will be defined as meeting at least three of five criteria: hypertension (blood pressure ≥130/85), hypertriglyceridemia (triglycerides >2 mmol/l), low HDL (HDL <1.295 mmol/l), central obesity (waist circumference >88 cm), or hyperglycemia (plasma glucose >7.8 mmol/l) (Figure 2).

Extended MetS will be defined as meeting at least 3 of the five criteria: hypertension (blood pressure ≥130/85), hypertriglycemia (triglycerides >2 mmol/l or LDL >3 mmol/l), low HDL (HDL <1.295 mmol/l), adiposity (waist circumference >88 cm, BMI ≥30, or WHR >0.85), or hyperglycemia (plasma glucose >7.8 mmol/l or HbA_1c_ ≥42 mmol/mol).

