### Outcomes

The primary outcomes were selected to address whether initiation of ET is associated with early changes in overall metabolic health. Given the short-term follow-up and the aim to capture early, potentially subtle metabolic alterations, the primary outcomes include an anthropometric and a composite metabolic measure.

The primary outcomes are:

Change in mean BMI from baseline to 3-month follow-upChange in mean MetS-Z from baseline to 3-month follow-up

BMI was chosen because weight changes are a well-known sideeffect of ET and may occur early following ET initiation, representing a clinically meaningful marker of metabolic health. Although short-term changes may be modest, even small increases may indicate emerging metabolic vulnerability. As a continuous composite measure, the widely used MetS-*z* score was selected to capture multidimensional metabolic changes that may not be reflected by individual metabolic parameters alone [21-24,29].

Secondary outcomes were selected to further characterize early metabolic changes and to compare expanded and conventional approaches to metabolic health classification.

The secondary outcomes include:

Change in the prevalence of MetS from baseline to 3-month follow-upComparison of the prevalence of MetS and extended MetS at 3-month follow-upChange in mean EMETA score from baseline to 3-month follow-upChange in mean values of individual metabolic parameters from baseline to 3-month follow-up, including waist circumference, hip circumference, WHR, blood pressure, and circulating levels of HbA_1c_, total cholesterol, triglycerides, LDL cholesterol, HDL cholesterol, and estradiol

The extended MetS and EMETA score are included as exploratory outcomes to assess whether broader composite measures capture early metabolic changes not identified by conventional definitions. Analysis of individual metabolic parameters provides insight into which metabolic domains are most affected shortly after ET initiation.

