### Analytical Approach

Statistical analyses will be conducted using Stata (version 18.5), with a 5% significance level for hypothesis testing. Changes in continuous primary outcomes (BMI and MetS-*z* score) will be analyzed using linear regression or linear mixed-effects models, as appropriate, to estimate mean within-person changes from baseline to 3-month follow-up. Changes in secondary continuous outcomes, including the EMETA score and individual metabolic parameters, will be analyzed using similar regression-based approaches. Changes in categorical outcomes (MetS and Extended MetS prevalence) will be analyzed using logistic regression models.

To account for exposure heterogeneity and treatment-related confounding, type of ET (tamoxifen vs aromatase inhibitor) and prior cancer treatments with potential metabolic impact, including neoadjuvant or adjuvant chemotherapy and supportive corticosteroid use, will be included as covariates in all adjusted analyses.

To address the secondary research question of whether certain patients are more vulnerable to early metabolic health deterioration following the initiation of ET, exploratory subgroup analyses will be conducted across both primary and secondary outcomes. These analyses will examine whether metabolic changes differ according to baseline and treatment-related characteristics, including age, BMI category, baseline metabolic status, menopausal status, type of ET, prior chemotherapy, smoking status, and comorbidity score. These subgroup analyses will be considered hypothesis-generating. Missing data will be assessed for randomness and extent. If data are missing at random, appropriate methods such as multiple imputation or mixed-effects models will be applied. Sensitivity analyses will be conducted to evaluate the potential impact of missing data on the study’s primary and secondary outcomes.

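### Extended MetS contains MetS by construction, so comparing the two prevalences at 3 months shows how much wider the definition is, not whether it captures early change

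*Protocol article*

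**What the plan says.** Definition of Analytic Values gives both rules. The conventional one reads "MetS will be defined as meeting at least three of five criteria: hypertension (blood pressure ≥130/85), hypertriglyceridemia (triglycerides >2 mmol/l), low HDL" below 1.295 mmol/l, waist above 88 cm, or plasma glucose above 7.8 mmol/l. The extended one reads "Extended MetS will be defined as meeting at least 3 of the five criteria: hypertension (blood pressure ≥130/85), hypertriglycemia (triglycerides >2 mmol/l or LDL >3". It leaves the HDL criterion as it was, widens the waist criterion to "adiposity (waist circumference >88 cm, BMI ≥30, or WHR >0.85", and widens the glucose criterion to "hyperglycemia (plasma glucose >7.8 mmol/l or HbA"1c of 42 mmol/mol or more.

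Outcomes lists, as a secondary outcome, a comparison of MetS and extended MetS prevalence at the 3-month visit. The same section says that the extended measures are included "to assess whether broader composite measures capture early metabolic changes not identified by conventional definitions". It lists change from baseline for MetS prevalence and for the EMETA score, but not for extended MetS prevalence.

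Analytical Approach adds: "Changes in categorical outcomes (MetS and Extended MetS prevalence) will be analyzed using logistic regression models". It sets a general 5% level but names no method for the 3-month comparison between the two definitions.

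**The concern.** Comparing conventional with expanded classification is one of the two stated aims, and the 3-month prevalence comparison is the only listed outcome that sets the two classifications directly against each other. If one definition contains the other, the direction of that comparison is settled before any data are seen. If the comparison also uses a single visit, a woman who was already extended-positive before treatment counts the same as one who became so afterwards.

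The risk lies in interpretation. The Discussion anticipates that extended and continuous measures may pick up early alterations that conventional MetS misses. A higher extended MetS prevalence at 3 months could be read as support for that when it reflects only the wider criteria.

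**Working it through.** **The plan's own figures.** The document gives no expected prevalence or power for this comparison. Its one power figure is for BMI and can be reproduced: 0.8 / (3/√112) = 2.82, and Φ(2.82 − 1.96) = 80.6% by the normal approximation (79.9% with the paired t). It has no bearing on this point.

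**Step 1: the two rules side by side** (Definition of Analytic Values).

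| Domain | MetS | Added in extended MetS |
|---|---|---|
| Blood pressure | ≥130/85 | nothing |
| Lipid | TG >2 | or LDL >3 |
| HDL | <1.295 | nothing |
| Adiposity | waist >88 | or BMI ≥30, or WHR >0.85 |
| Glycaemia | glucose >7.8 | or HbA1c ≥42 |
| Count needed | 3 of 5 | 3 of 5 |

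Every domain met under MetS is also met under extended MetS, so the extended count is never lower. As a check, all 2^9 = 512 true/false patterns of the nine thresholds were scored under both rules: 256 positive on both, 162 extended-only, 94 negative on both, and 0 MetS-only. These are counts of logical patterns, not expected frequencies. The result is the same if extended MetS is read as any 3 of nine separate criteria, and whether the blood pressure criterion means 'and' or 'or'.

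**Step 2: what the 3-month difference measures.** At one visit, in the same n women,

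prevalence(extended) − prevalence(MetS) = (extended-only − MetS-only)/n = extended-only/n ≥ 0.

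No baseline term enters. Take a woman with the same values at both visits: blood pressure 132/86, TG 0.9, LDL 3.1, HDL 1.8, waist 80 cm, BMI 23, WHR 0.86, glucose 5.5, HbA1c 36. She meets 1 of 5 MetS criteria (blood pressure) and 3 of 5 extended criteria (blood pressure, LDL, WHR). She adds to the 3-month gap although nothing has changed.

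**Step 3: what a contrast of changes would measure.** Let D be the extended-only share at a visit. Then

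change(extended) − change(MetS) = D at 3 months − D at baseline.

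This can be positive, zero or negative. The woman above contributes 1 − 1 = 0. A woman negative on both at baseline and extended-only at 3 months contributes +1. One who moves from extended-only to MetS contributes −1, because only the conventional definition registered her change.

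**Step 4: if a paired test of equality were applied.** This is an assumption, since the document names no test. With all discordant pairs in one direction, the exact two-sided McNemar p is 2 × 0.5^k:

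- k = 5: 2 × 0.5^5 = 0.063
- k = 6: 2 × 0.5^6 = 0.031, with 6/112 = 5.4% of the cohort

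**Step 5: how likely 6 or more would be.** The document gives no criterion prevalences, so three sets were assumed, with independent criteria and no change over time. The order is blood pressure, TG, HDL, waist, glucose; then LDL, BMI-or-WHR, HbA1c. In the middle set, for example, the widened lipid criterion has prevalence 1 − (0.80 × 0.70) = 0.44.

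| Assumed prevalences (%) | MetS | Extended | Extended-only | P(≥6 of 112) |
|---|---|---|---|---|
| 30, 15, 15, 30, 3; 20, 5, 2 | 4.0% | 7.5% | 3.5% | about 20% |
| 40, 20, 20, 40, 5; 30, 10, 5 | 9.0% | 17.8% | 8.8% | 93% |
| 50, 25, 20, 50, 5; 50, 20, 10 | 14.2% | 33.1% | 18.9% | >99% |

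The last column is the binomial upper tail for 112 women at the extended-only share.

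**The case against.** Four counter-arguments deserve weight.

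- **The document specifies no test of equality.** It promises a comparison of prevalences, and an article may leave the method to a fuller plan. This stands. The p = 0.031 figure shows what would follow from one possible analysis and is not a defect in a stated one.
- **The size of the gap is informative although its sign is fixed.** How many more women the wider definition labels unhealthy is a fair descriptive question under the second aim, and the Abstract says openly that the definition is an expansion. This stands, and it is why the comparison should be kept. A reader might infer that it is empty; the documents do not support that.
- **Early change is addressed elsewhere.** Analytical Approach covers change in both prevalences, and change in MetS-Z and in the EMETA score are listed outcomes. A reader might infer that the study cannot examine early change with the extended measures; that would be wrong. What remains is narrower: change in extended MetS prevalence is missing from the outcome list, and no contrast of the two changes is stated.
- **The extended measures are labelled exploratory**, and the Discussion leaves validation to later studies. This limits the consequence, but an exploratory comparison should still be able to answer the question set for it.

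It is also tempting to say that extended MetS is almost certain to come out significantly higher. The document gives no distributions to support that, and the lowest assumed scenario puts the chance at about 20%.

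**Conclusion.** The point holds in a limited form. Containment is exact and follows from the definitions alone, provided that both are scored on the same women with complete components. The 3-month difference therefore equals the extended-only share, cannot be negative, and carries no information on change since baseline. It describes how much wider the extended definition is, and does not by itself serve the purpose given in Outcomes.

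The significance arithmetic (6 of 112, p = 0.031) is firm only if a two-sided exact paired test is used. The probability of reaching that number rests wholly on assumed prevalences. The weakness is confined to one secondary, exploratory comparison.

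**What to change.** - Keep the 3-month comparison but make it descriptive: report the extended-only share at baseline and at 3 months, each with a confidence interval, and no test of equality.
- State in the methods and beside the result that extended MetS contains MetS by definition.
- Add change in extended MetS prevalence to the listed outcomes, to match Analytical Approach.
- Add the paired difference between the two changes (new minus resolved cases under each definition) with a confidence interval, for example by bootstrap over women. Label it exploratory and as added before analysis, provided that analysis has not begun.

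No new data are needed, because the components are measured at both visits. The cost is one more exploratory analysis and a notification to the ethics committee and registry, as Ethical Considerations describes for changes to outcomes or methods. The result will probably be less striking, with a wide interval. Dropping the listed comparison after follow-up has ended would be harder to defend and is not needed.

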**Figure 2. F2:**
[figure not shown]
Comparison of MetS, extended MetS, MetS-Z, and EMETA scores. Red text: Variables specific to the extended MetS and EMETA score. HDL: High-density lipoprotein, LDL: Low-density lipoprotein. HbA_1c_: Hemoglobin A_1c_. Created in BioRender. [name] (2025) https://BioRender.com/

#### *z* Score Calculations

The MetS-*z* score will be calculated as a standardized composite score of the five MetS components. Standardization will be achieved by subtracting ATP III criteria from each individual’s value of waist circumference (WC), triglycerides (TG), middle arterial pressure (MAP), plasma glucose (PG), and inverted HDL, dividing by the baseline cohort standard deviation (σ).

(1)
$$MetS\text{-}Z=\frac{WC-88}{\sigma_{wc}}+\frac{TG-2}{\sigma_{TG}}+\frac{MAP-100}{\sigma_{MAP}}+\frac{PG-7.8}{\sigma_{PG}}-\frac{HDL-1.295}{\sigma_{HDL}}$$

The EMETA score is a exploratory composite *z* score that will be calculated using the same approach as MetS-*z* score, based on the extended MetS components.

(2)
$$\begin{array}{rl} \text{EMETA}= & \frac{WC-88}{\sigma_{WC}}+\frac{BMI-30}{\sigma_{BMI}}+\frac{WHR-0.85}{\sigma_{WHR}}+\frac{TG-2}{\sigma_{TG}}\\ -\frac{HDL-1.295}{\sigma_{HDL}}+\frac{LDL-3}{\sigma_{LDL}}+\frac{MAP-100}{\sigma_{MAP}}+\frac{PG-7.8}{\sigma_{PG}}+\frac{HbA1c-42}{\sigma_{HbA1c}} \end{array}$$

#### Covariables

Information on the following co-variables has been collected from medical records and will be included in adjusted analyses. These include patient demographics: age, weight, height, Carlson Comorbidity score (0, 1‐2, 3‐4, ≥5), current comorbidities (none, cardiopulmonary disease, neurological, dyslipidemia, musculoskeletal, other cancers, abdominal, urogenital, endocrine, dermatological, others), smoking status (never smoker, former smoker, active smoker), civil status (living alone, living with a partner), and area of living (rural/city). Cancer-specific characteristics: date of breast cancer diagnosis, disease stage (T+N), human epidermal growth factor receptor 2 status, histological type, grade of malignancy, and previous breast cancer history. Treatment modalities included duration and type of neo-adjuvant and adjuvant therapy (including supportive prednisolone treatment), date of breast cancer surgery, and radiotherapy.

### Analytical Approach

Statistical analyses will be conducted using Stata (version 18.5), with a 5% significance level for hypothesis testing. Changes in continuous primary outcomes (BMI and MetS-*z* score) will be analyzed using linear regression or linear mixed-effects models, as appropriate, to estimate mean within-person changes from baseline to 3-month follow-up. Changes in secondary continuous outcomes, including the EMETA score and individual metabolic parameters, will be analyzed using similar regression-based approaches. Changes in categorical outcomes (MetS and Extended MetS prevalence) will be analyzed using logistic regression models.

To account for exposure heterogeneity and treatment-related confounding, type of ET (tamoxifen vs aromatase inhibitor) and prior cancer treatments with potential metabolic impact, including neoadjuvant or adjuvant chemotherapy and supportive corticosteroid use, will be included as covariates in all adjusted analyses.

To address the secondary research question of whether certain patients are more vulnerable to early metabolic health deterioration following the initiation of ET, exploratory subgroup analyses will be conducted across both primary and secondary outcomes. These analyses will examine whether metabolic changes differ according to baseline and treatment-related characteristics, including age, BMI category, baseline metabolic status, menopausal status, type of ET, prior chemotherapy, smoking status, and comorbidity score. These subgroup analyses will be considered hypothesis-generating. Missing data will be assessed for randomness and extent. If data are missing at random, appropriate methods such as multiple imputation or mixed-effects models will be applied. Sensitivity analyses will be conducted to evaluate the potential impact of missing data on the study’s primary and secondary outcomes.

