## Discussion

This study is anticipated to indicate that initiation of ET in women with ER+ EBC will be associated with modest early metabolic changes over the first three months of treatment. These changes may include small increases in BMI and selected lipid-related parameters, while markers with longer biological response times, such as HbA_1c_, may show minimal or no short-term change. Extended and continuous measures of metabolic health may capture early alterations not identified by conventional MetS definitions. Importantly, these analyses are exploratory and intended to evaluate sensitivity and feasibility rather than to establish clinical thresholds or predictive value.

Previous studies have linked ET with weight gain, insulin resistance, and dyslipidemia, all of which increase cardiovascular risk and may impact breast cancer outcomes [5,10-12,14,32]. However, most prior work has focused on longer-term outcomes or relied on dichotomous classifications. By evaluating both conventional and expanded measures within a short-term framework, this study contributes to understanding how early metabolic changes may be characterized following ET initiation.

Key strengths of this study include its prospective design with paired baseline and 3-month follow-up data, allowing within-subject comparison of early metabolic changes. The use of both conventional and expanded metabolic measures enables comparison of different classification approaches and addresses known limitations of binary definitions. The short follow-up period and alignment with routine clinical care minimize additional participant burden, supporting broad inclusion and reducing the risk of selection bias related to study participation.

The study is conducted at a single center, which may limit generalizability beyond similar healthcare settings. Exclusion of patients with pre-existing diabetes, while necessary to reduce baseline metabolic confounding, restricts applicability to a population that commonly receives endocrine therapy. In addition, although efforts were made to minimize attrition, informative dropout cannot be excluded, particularly if early metabolic or treatment-related symptoms influenced follow-up participation. The modest sample size limits power for subgroup analyses, which are therefore considered exploratory.

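### EMETA is MetS-Z plus four added terms, but the changes in the two scores are analysed only separately, so those two analyses alone cannot isolate what the added variables contribute

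*Protocol article*

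**What the plan says.** The Outcomes section makes mean change in MetS-Z a primary outcome and mean change in EMETA a secondary one. It gives the purpose of the extended measures as to "assess whether broader composite measures capture early metabolic changes not identified by conventional definitions". The Objective and the aim at the end of the Introduction both include comparing conventional with expanded approaches, and the Methods part of the Abstract counts MetS-Z among the conventional measures.

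Under z Score Calculations, "The MetS-*z* score will be calculated as a standardized composite score of the five MetS components", each term being formed by "dividing by the baseline cohort standard deviation". EMETA is a score "that will be calculated using the same approach as MetS-*z* score, based on the extended MetS components".

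For analysis, the Analytical Approach models change in BMI and MetS-Z first and then states: "Changes in secondary continuous outcomes, including the EMETA score and individual metabolic parameters, will be analyzed using similar regression-based approaches". The individual parameters include "waist circumference, hip circumference, WHR, blood pressure, and circulating levels of" HbA1c and the lipids, LDL among them. BMI is itself a primary outcome. The only head-to-head comparison listed is between the two binary definitions, MetS and extended MetS, as prevalence at 3 months.

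**The concern.** The two continuous scores are nested: one is the other plus a block of four terms. If each total is analysed on its own, the results answer whether MetS-Z changed and whether MetS-Z plus the block changed. Neither answers whether the block added anything.

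This can mislead in two directions. If only the shared terms move, EMETA may be significant and the added variables may get the credit. If only the added terms move, the variability of the five shared terms enters the EMETA total and can bury the change. A significant result for one total and a non-significant result for the other is not a test of the difference between them.

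At stake is the continuous-score half of the study's comparison aim. The primary outcomes are not affected.

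**Working it through.** **The plan's own figure.** Cohort Size gives more than 80% power for a BMI change of 0.8 with SD of change 3 and n = 112. The paired normal approximation is Φ(0.8 × √112 / 3 − 1.96) = 0.806, so it reproduces. It does not bear on this point. No power figure, SD or correlation is given for either score.

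**Step 1: nesting.** Terms in each formula:

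| Term | MetS-Z (eq. 1) | EMETA (eq. 2) |
|---|---|---|
| WC − 88, TG − 2, MAP − 100, PG − 7.8, −(HDL − 1.295), each over its baseline SD | yes | yes, identical |
| BMI − 30, WHR − 0.85, LDL − 3, HbA1c − 42, each over its baseline SD | no | yes |

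Hence D = EMETA − MetS-Z is the sum of the four added terms, and for each woman ΔEMETA = ΔMetS-Z + ΔD exactly.

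**Step 2: how strongly the totals overlap.** The documents give no SDs, so these are assumptions: SD of ΔMetS-Z s_M = 1.3-1.8, SD of ΔD s_D = 0.7-1.2, correlation ρ between them = 0-0.4, 112 complete pairs, two-sided 5%.

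- SD of ΔEMETA: s_E = √(s_M² + s_D² + 2ρ s_M s_D)
- Correlation of ΔMetS-Z with ΔEMETA: (s_M + ρ s_D) / s_E
- Lowest corner (1.3, 1.2, ρ = 0): s_E = √3.13 = 1.769; 1.3 / 1.769 = 0.73
- Highest corner (1.8, 0.7, ρ = 0.4): s_E = √4.738 = 2.177; (1.8 + 0.28) / 2.177 = 0.96

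**Step 3: power if only the added block moves, by 0.25 in total.** The noncentrality is 0.25 × √112 / SD = 2.646 / SD, with noncentral-t power on 111 df.

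| Quantity tested | SD of change | Noncentrality | Power |
|---|---|---|---|
| EMETA, best corner (1.3, 0.7, ρ = 0) | 1.476 | 1.79 | 43% |
| EMETA, worst corner (1.8, 1.2, ρ = 0.4) | 2.531 | 1.05 | 18% |
| D, s_D = 0.7 | 0.7 | 3.78 | 96% |
| D, s_D = 1.2 | 1.2 | 2.20 | 59% |

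**Step 4: a second set of assumptions, term by term.** Each standardised term has SD of change 0.4-0.8, a common correlation of 0-0.4, and a shift of 0.1 where it moves.

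- Only the five shared terms move: EMETA rejects in 19-99% of studies and D in 5%. The 5% supposes that the shift in waist does not carry into WHR.
- Only the four added terms move: EMETA rejects in 14-94%, D in 42% to nearly 100%, a single added parameter in 26-75%.

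**Step 5: what planned outputs already give.** The point estimate of mean ΔD can be recovered by subtracting the two mean score changes, provided that both use the same women and the same model. Its standard error cannot, because it needs the covariances between terms. With term SD 0.6 it runs from 0.6 × 2 / √112 = 0.113 (correlation 0) to 0.6 × 4 / √112 = 0.227 (correlation 1), a twofold range.

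**The case against.** The strongest reply is that all four added variables have their own planned change analysis: BMI as a primary outcome, and WHR, LDL and HbA1c as secondary ones. A reader might infer from the nesting that the study cannot show at all whether the added variables move when MetS-Z does not. The documents do not support that. The single-parameter analyses address it variable by variable. What they lack is a joint estimate, with its uncertainty, for the block that distinguishes EMETA.

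A reader might also infer that the plan will treat one significant and one non-significant total as a difference. It nowhere says so. The Discussion's expectation that "Extended and continuous measures of metabolic health may capture early alterations not identified by conventional MetS definitions" can be read as a contrast with the binary definition, which places MetS-Z on the other side. The gap remains because the Abstract labels MetS-Z conventional and the comparison aim is not limited to the binary measures.

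It is also tempting to make D the deciding test. That would be unsound. WHR is waist over hip, so a pure waist change moves both MetS-Z and D. Opposite movements, such as BMI up and LDL down, cancel in D. And a non-zero D shows that the block moved, not that MetS-Z missed the change.

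Finally, EMETA is labelled exploratory throughout, and an analysis plan that is not shown could add the contrast. This limits the weight of the point. But the article does state a method for EMETA, and that method alone does not match the purpose given for the score.

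**Conclusion.** The point holds in a limited form. The nesting is exact, and the two score analyses alone cannot separate the added variables' contribution from that of the shared terms. The single-parameter analyses partly fill the gap but give no joint inference on the added block.

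In size, the changes in the two totals would correlate at about 0.73-0.96. For an added-block change of 0.25, the EMETA total would have about 18-43% power against 59-96% for D. These figures rest wholly on assumed SDs and correlations and on complete follow-up of 112 women. The nesting itself rests on no assumption. As the score is exploratory and the primary outcomes are untouched, this is an inexpensive improvement that is worth making, not a flaw that undermines the study.

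**What to change.** Add to the Analytical Approach, before the results are seen:

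- Estimate the mean within-woman change in D = EMETA − MetS-Z (the sum of the standardised BMI, WHR, LDL and HbA1c terms) with the same model as the scores, and report it with a 95% CI.
- Beside it, show each term's standardised contribution to the mean change and the single-parameter results. With the same women and the same model, the contributions add up to the change in the composite.
- State that a change in one total but not the other will not be read as a difference between the scores.
- Attach no pass/fail rule to D. Note that WHR shares waist with MetS-Z and that opposite movements of the added terms can cancel.

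The cost is one more exploratory analysis of a variable derived from data already held, and a few sentences of text.
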